### Secondary outcomes

For secondary outcomes, we will adhere to the criteria proposed to evaluate the legalization of cannabis in Canada
^41^, encompassing all cannabis use behaviours linked to adverse consequences, for which substantial evidence exists
^32^. As intervention group participants will receive information on risky cannabis use
^32^ and enclosed within each cannabis package sold by the pharmacies, we hypothesize that risky cannabis use practices will not increase among these users – despite the presumably increased availability of cannabis products. Specifically, we hypothesize that intervention group participants will: A) not increase their use frequency, B) not increase frequency of THC-impaired driving, and C) will not smoke cannabis products more frequently (for operationalization, see
Table 1). The secondary outcomes will be evaluated at one-year follow-up, which involves testing for differences between control and intervention group while taking baseline values into account.

**Table 1. T1:** Operationalization of secondary outcomes.

Indicator	Operationalization
A) Frequency of use	Number of use days in the past 30 days
B) THC-impaired driving	Number of occasions on which a vehicle was driven within six hours after using cannabis in the past 30 days
C) Mode of administration	Percentage of all use units using combustible methods, such as smoking joints, blunts, (water) pipes

As further secondary outcomes, we will examine acceptance and satisfaction of the dispensary model among intervention group participants, which may be important for explaining a possible dominance of illegal over legal consumption (see first aspect of primary outcome).

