^38^ met the outlined criteria (cap of potency and cap of THC/CBD ratio) to be sold to the intervention group participants in this study. As prescribed for medical cannabis, each batch of herbal cannabis will undergo routine pharmaceutical tests. Further, producers of medical marijuana are legally required to perform systematic tests to detect variations in potency levels and contaminants. In accordance with the requirements of the narcotics law, cannabis stored in the pharmacies will not be accessible to anyone but trained staff. All cannabis products will be stored in a steel cabinet protected by a safety lock, in accordance with the standards prescribed by the German ‘Federal Institute for Drugs and Medical Devices’ (Bundesinstitut für Arzneimittel und Medizinprodukte,
BfArM).

In all participating pharmacies, users will find printed information material on mitigating use risks and will be offered the option of renting devices for vaporizing herbal cannabis. The use of vaporizers can reduce exposure to some hazardous compounds and is hence considered a harm-reducing method
^39^. Further, the vending staff in all participating pharmacies will be trained in the following: legal framework, safer use guidelines (original:
^32^, for a German translation:
^40^), identification of vulnerable users, cooperation with drug counselling and prevention services. If required, study participants will be able to hold conversations with staff in private on the pharmacy premises.

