Multilevel regression analyses will be performed additionally for evaluating the primary outcome, which serve to rule out the impact of possibly confounding variables. For evaluating the secondary outcomes, the proposed analyses (correction for baseline values, comparison via t-test, confirmation via multilevel regression analyses) will be performed analogously.

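### Secondary hypothesis C is about how often participants smoke, but Table 1 measures the combusted share of use units, which cannot by itself settle that question

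*Protocol article*

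**What the plan says.** The Secondary outcomes section of the protocol article sets a general hypothesis: "we hypothesize that risky cannabis use practices will not increase among these users", even though availability is presumed to rise. Three specific hypotheses follow, with Table 1 giving the measure for each.

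- **Outcome A** is a tally of days: "Number of use days in the past 30 days".
- **Outcome B** is a tally of driving episodes: "Number of occasions on which a vehicle was driven within six hours after using cannabis in the past 30 days".
- **Outcome C** carries the label mode of administration. The hypothesis is that participants "will not smoke cannabis products more frequently"; the measure is "Percentage of all use units using combustible methods, such as smoking joints, blunts, (water) pipes".

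A and B are counts that match their hypotheses. C alone is a proportion.

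Sample size and data analyses fixes the method: "For evaluating the secondary outcomes, the proposed analyses (correction for baseline values, comparison via t-test, confirmation via multilevel regression analyses) will be performed analogously". Details of the dispensary model adds that users of the participating pharmacies will be "offered the option of renting devices for vaporizing herbal cannabis".

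**The concern.** Hypothesis C asks whether smoking becomes more frequent once cannabis can be bought legally. A share of use units answers a different question: of what is used, how much is burned. If legal access adds vaporized units on top of existing smoking, the denominator grows and the share falls even when smoking is unchanged or rising. The design makes this plausible in one group only, because the vaporizer rental and the legal supply both belong to the intervention.

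At stake is the wording of a harm conclusion. A favourable result on the share could be reported as no more frequent smoking when the number of smoked units had gone up.

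**Working it through.** The plan states no figure for this outcome, so there is nothing to reproduce. The check is arithmetic on the definition in Table 1. All unit counts below are assumptions chosen for illustration; the article gives none.

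**Definition.** Let C be combusted units, N other units and T = C + N. The planned measure is the share p = C/T, so C = p × T.

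**Condition.** Going from T0 to T12, C rises when p1 × T1 > p0 × T0, that is, when T1/T0 > p0/p1. For a falling share (p1 < p0), smoking therefore rises despite the better-looking indicator once total units grow by more than p0/p1 − 1. If the share rises, the indicator moves up and this error does not arise.

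| Share at T0 → T12 | Growth in total units above which smoking rises |
|---|---|
| 100% → 90% | 1/0.9 − 1 = 11.1% |
| 90% → 80% | 0.9/0.8 − 1 = 12.5% |
| 100% → 80% | 1/0.8 − 1 = 25% |
| 90% → 70% | 0.9/0.7 − 1 = 28.6% |
| 80% → 60% | 0.8/0.6 − 1 = 33.3% |

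**Worked cases.**

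| Units at T0 (combusted + other) | Units at T12 | Share | Smoked units |
|---|---|---|---|
| 20 + 0 | 24 + 6 | 100% → 80% | 20 → 24 (+20%) |
| 20 + 5 | 24 + 12 | 80% → 66.7% | 20 → 24 (+20%) |
| 20 + 5 | 15 + 0 | 80% → 100% | 20 → 15 (−25%) |

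In the first two cases the share improves while smoking rises. In the third it worsens while smoking falls.

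**Effect of the planned analysis.** If the baseline correction printed for the primary outcome (T12 value × 100 / T0 value) is carried over to C, the first case scores 80 × 100/100 = 80 and the third scores 100 × 100/80 = 125. Against an unchanged participant at 100, the one who smokes more looks better and the one who smokes less looks worse.

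**Could another outcome supply the count?**

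- *Outcome A* counts days and cannot exceed 30. Units per day can rise with A unchanged, most plainly in a daily user.
- *The primary outcome* is built from THC per usual unit and the number of use occasions (Assessment details), so it responds to volume but also to potency. Suppose units rise 15%, the share falls from 100% to 90%, and THC per unit falls 22%. Total THC is then 1.15 × 0.78 = 0.897 of baseline, about 10% lower, while smoked units are 1.15 × 0.90 = 1.035 of baseline, 3.5% higher.

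**The case against.** Table 1 defines the endpoint without ambiguity, and its label, mode of administration, fits a share. A share separates how cannabis is used from how much. A count mixes the two, so a fall in smoked units from using less would look the same as switching to a vaporizer, which is the harm-reducing step the programme offers. On this view the fault is a loosely worded phrase. That stands as a reason to keep the share and as an argument that rewording the hypothesis is a legitimate remedy. It does not remove the mismatch: the text states a frequency under a general hypothesis of no increase, and nothing in it says that frequency is meant relative to other modes.

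The second objection is that a rise in volume would not go unseen. The questionnaire collects use occasions over the past 30 days, and these feed the primary outcome. Treating a unit as an occasion, growth from 20 to 30 units (+50%) would satisfy the primary condition of at most 0.9 times control, with control unchanged, only if THC per unit fell to 0.9/1.5 = 0.6 of baseline, a 40% drop. This stands for large rises. A reader might infer that increased smoking would escape the trial altogether, and the article does not support that. The protection is partial, though: smaller rises can be offset by lower potency, which the dispensary model promotes through its THC cap and pricing, and THC exposure does not distinguish smoked from vaporized use.

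A reader might also assume that the count is already in hand because it is the numerator of the percentage. The adapted DFAQ-CU items are not shown, and respondents may be asked for a percentage or usual mode directly.

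**Conclusion.** The point holds as a mismatch between hypothesis and measure. The combusted share cannot by itself support a conclusion about how often participants smoke, and no other listed outcome counts smoked units or occasions. With a falling share, growth in total units of about 11% to 33% is enough to reverse the reading over the range of share changes tabulated; an error in the opposite direction is equally possible.

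Those figures follow from the definition, but the share changes and unit counts are assumptions. The article gives no basis for saying how large the discrepancy will be, or that smoking will in fact rise under legal access. The consequence is confined to one of the three behavioural secondary outcomes. The primary outcome, the sample size and the rule for overall success are unaffected.

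**What to change.** Test hypothesis C on the number of combusted use units or occasions in the past 30 days, and keep the percentage beside it as the measure of mode of administration. The count can be asked directly in the questionnaire, or derived as the combusted share times the use occasions already collected. The derived version treats a use unit as a use occasion, which should be stated.

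If a count is not adopted, reword hypothesis C and its conclusion to the share of combusted use, so that a result on the share is not reported as a result on smoking frequency.

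The cost is an amended row in Table 1, one extra secondary analysis and possibly one adapted questionnaire item. The count also mixes mode with volume, which is why the share should stay alongside it.

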### Sample size and data analyses

The study outcomes will be analysed according to ‘Intention-to-treat’ (ITT) principles. Specifically, the sample to be analysed is defined as all users who have provided a usual consumption unit within 4 weeks after completing the baseline questionnaire. Over-recruitment will compensate for participants failing to provide a consumption unit within this period. According to ITT principles, only those participants who provided their baseline data, including their usual consumption unit, will be included in the analyses.

To examine between-group differences with a t-test, the required sample size of this study was calculated assuming a power of 80%, a 5% alpha error, and a THC standard deviation equal to one-third of its mean (approximated using Canadian data,
^43^; adding 25% to account for uncertainty). The required sample size was estimated to sum up to n=698 participants (control: n=349; intervention: n=349) for detecting group differences in THC exposure.

Not relevant for sample size considerations, we expect that 20% (control: 30%; intervention: 10%) of all participants of the ITT sample will be lost to T12 follow-up. Subjects dropping out of the study will not be replaced and missing values will be imputed using the ‘Last Observation Carried Forward‘ (LOCF) technique. The critique regarding LOCF imputation methods
^44^ does not apply to our study, as this method will bias the data towards the null hypothesis (assuming no change over time) and therefore representing a conservative imputation approach. The assumptions of LOCF will be examined in sensitivity analyses using advanced multiple imputation techniques.

To evaluate both aspects of the primary outcome, two analyses need to be conducted. First, the THC exposure levels in the past 30 days ascribed to illegal cannabis acquisition within the intervention group needs to be compared between baseline and intervention, with a 50% reduction denoting the minimum threshold for a positive evaluation. Second, a between-group comparison of THC exposure in the past 30 days at T12 adjusting for baseline data will be conducted using a t-test. The dependent variable will be calculated as follows:

$$THC_{T12–adjusted}=\frac{THC_{T12}*100}{THC_{T0}}$$

The actual between-group comparison will be evaluated against the following condition:

$$THC_{T12–adjusted–interventiongroup}<=0.9*THC_{T12–adjusted–control\;group}$$

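### Secondary hypotheses A–C claim no increase in risky use, but the planned t-test for a difference, with no margin, cannot support that claim

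*Protocol article*

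**What the plan says.** The Secondary outcomes section of the protocol article sets the direction: "we hypothesize that risky cannabis use practices will not increase among these users". It then lists three hypotheses for intervention participants: "A) not increase their use frequency, B) not increase frequency of THC-impaired driving, and C) will not smoke cannabis products more frequently". Table 1 defines these as use days in the past 30 days, occasions of driving within six hours of use, and the percentage of use units that are combusted.

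The same section says how they will be judged: "The secondary outcomes will be evaluated at one-year follow-up", which "involves testing for differences between control and intervention group while taking baseline values into account". The end of Sample size and data analyses names the procedure: "the proposed analyses (correction for baseline values, comparison via t-test, confirmation via multilevel regression analyses) will be performed analogously".

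No tolerable increase, confidence-interval rule or power is given for A–C. The two numerical criteria in Sample size and data analyses (a 50% reduction and a factor of 0.9) belong to the two primary aspects, and neither appears among the analyses carried over. That section also imputes missing values by LOCF, defended as conservative because it favours the null of no change, with multiple imputation as a sensitivity analysis. Expected loss by month 12 is 10% in the intervention group and 30% in the control group.

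**The concern.** A difference test takes no difference as its null hypothesis. It can reject that null but cannot establish it. For A–C, the statement the investigators want to support lies on the null side, so the planned test gives evidence against the hypotheses or no verdict, never evidence for them. The noisier the outcome, the likelier the result that looks favourable.

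Two features add to this. First, bias towards no change is cautious for a hypothesis of change, but for a hypothesis of no increase it pushes in the hoped-for direction. Second, A–C are worded as change within the intervention group but tested between groups, so an equal rise in both cities would show no difference.

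At stake is the reassurance that legal access does not raise risky use. The Conclusion section expects the findings to inform regulation in Germany and elsewhere.

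**Working it through.** **The plan's own sample size.** It gives 349 per group for THC exposure, with "assuming a power of 80"%, "a 5% alpha error" and "a THC standard deviation equal to one-third of its mean", plus a 25% allowance. The effect is not stated in that paragraph; 10% of the mean is taken from the primary hypothesis. With n per group = 2 × (SD × 2.8016 / 0.10)², where 2.8016 = 1.96 + 0.8416:

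- SD 1/3: 174.4, so 175.
- SD 1/3 × 1.25 = 0.4167: 272.5, so 273.

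Neither gives 349. The present point does not depend on this; 349 is taken as given.

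**Inputs for A–C.** The documents give no SD and no margin for these outcomes, so everything below is in SD units over an assumed range. The test is taken as two-sided 5%, since sidedness is not stated.

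**Step 1: precision.** SE = √(1/n₁ + 1/n₂).

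- Full sample: √(2/349) = 0.0757 SD; 95% half-width 1.96 × 0.0757 = 0.148 SD.
- Expected completers, 349 × 0.9 ≈ 314 and 349 × 0.7 ≈ 244: SE = 0.0853 SD; half-width 0.167 SD.

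**Step 2: chance of a non-significant result despite a true rise d.** This is Φ(1.96 − d/SE).

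| True rise | 349 + 349 | 314 + 244 |
|---|---|---|
| 0.10 SD | Φ(0.64) = 74% | 78% |
| 0.15 SD | Φ(−0.02) = 49% | 58% |
| 0.20 SD | Φ(−0.68) = 25% | 35% |

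**Step 3: baseline adjustment.** Covariate adjustment with baseline–month-12 correlation r shrinks the SE by √(1 − r²). The documents give no r. At 349 per group, assuming r = 0.5 (factor 0.866) and r = 0.7 (factor 0.714), the 74% becomes 67% and 54%, the 49% becomes 37% and 21%, and the 25% becomes 14% and 4%. A ratio correction like that used for THC need not behave this way.

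**Step 4: LOCF.** Suppose use rises by d in the intervention arm, controls are stable, dropouts would have risen as completers did, and every dropout carries a baseline value forward. The arm then shows 0.9d. At 349 per group, Φ(1.96 − 0.9d/0.0757) gives 78%, 57% and 34% for d = 0.10, 0.15 and 0.20 SD. These are upper bounds: questionnaires are also taken at T3 and T6, so some carried values would already contain the rise.

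**Step 5: what a matching test could show.** With a one-sided 2.5% non-inferiority test and a true difference of zero, the smallest margin with 80% power is 2.8016 × SE:

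- 349 + 349: 2.8016 × 0.0757 = 0.21 SD.
- 314 + 244: 2.8016 × 0.0853 = 0.24 SD.

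For tighter margins, the n per group needed is 393 at 0.20 SD, 698 at 0.15 SD and 1,570 at 0.10 SD.

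**The case against.** The best defence is that the protocol nowhere says how a null result will be read. A reader might infer that a non-significant t-test will be presented as proof of no harm. No section states this, so the risk is one of misreading and not a declared rule. A related defence is that margins for secondary outcomes may sit in an analysis plan that is not shown. That also stands: the absence of a margin is not in itself the fault. What remains is that the article commits to a test whose form does not match the hypotheses, and offers no other criterion for supporting them.

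Three further readings go too far:

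- **That a real rise would usually be missed.** This holds only below about 0.15 SD without adjustment. A rise of 0.20 SD is detected in about 75% of trials, and nothing in the documents fixes what size of rise matters. Figures in use days would need an SD that the article does not give.
- **That LOCF dilutes a rise by up to 30%.** The 30% is the control-arm loss. A rise confined to the intervention arm is diluted only by that arm's 10%. If both arms shifted equally by c, full baseline carry-forward would show 0.9c − 0.7c = 0.2c, so LOCF can also work against the hypotheses when both arms rise.
- **That missing data and confounding are left unaddressed.** Multiple imputation and multilevel regression are both planned. Neither supplies a margin, so neither cures the mismatch.

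It is also fair to say that A–C do not decide the study's success, which the Primary outcome section ties to the two primary aspects alone.

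**Conclusion.** The point holds as a mismatch between hypothesis and test. A–C say that risky use will not increase; the stated analysis can find a difference but cannot support its absence. That conclusion comes from the text and needs no assumption.

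Its size is conditional: at 349 per group, a true rise goes undetected in about 74%, 49% and 25% of trials at 0.10, 0.15 and 0.20 SD. These figures assume a two-sided 5% test, a normal approximation, equal SDs and no gain from baseline adjustment; a usable baseline correlation would lower them. LOCF's stated conservatism does not carry over to A–C, but with stable controls its effect on a rise in the intervention arm is modest. The change should be made, at the weight due to secondary outcomes that carry a safety message.

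**What to change.** 1. Restate A–C as between-group non-inferiority hypotheses, and fix one justified margin per outcome, on a stated scale, before data collection.
2. Claim that an outcome has not increased only if the upper limit of the 95% confidence interval for the baseline-adjusted difference (or the rate ratio for impaired driving) lies below its margin. Otherwise report the estimate and interval as inconclusive.
3. Base that claim on the multiple imputation already planned as a sensitivity analysis, not on LOCF alone, and drop the argument that LOCF is conservative for these outcomes.

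The cost is wording and three margins, with no added participants. The real price is that some outcomes may end as inconclusive: with a true difference of zero, 80% power is reached only for margins of about 0.21 SD, or 0.24 SD with the expected completers, unless baseline adjustment improves precision. Whether margins of that width are acceptable must be argued for each outcome; the calculation does not settle it.

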### Assessment details

For both aspects of the primary outcome, THC exposure within the past 30 days needs to be determined for each respondent by combining the following data sources. First, THC levels per average use occasion will be determined through analyses of usual consumption samples provided at both baseline and after one year (T12). Second, questionnaire data will be used to determine the number of use occasions within the past 30 days, separately for legally and illegally acquired cannabis. Third, and only for the intervention group, sales data will be used to determine THC exposure levels of legally acquired cannabis over a 12-month period.

In summary, for the control group, THC exposure levels within the past 30 days will be determined multiplying THC levels in a usual consumption unit with the number of use occasions reported in the questionnaire. For the intervention group, THC exposure levels will be determined analogously while correcting for the proportion of legally acquired and consumed THC using sales and questionnaire data.

At all waves — T0, T3, T6, and T12 — a set of questionnaires will be administered (see
Table 2). For the primary and secondary outcomes, use characteristics will be assessed using items from the ‘Daily Sessions, Frequency, Age of Onset, and Quantity of Cannabis Use Inventory’ (DFAQ-CU), which will be translated and adapted for this study. All remaining questionnaire data will serve to explain unexpected findings, to control for potential confounders in the statistical analyses, or for the economic evaluation of this study.

**Table 2. T2:** Summary of questionnaire assessment.

Indicator	Questionnaire or item source
Cannabis use characteristics, for primary and secondary outcomes	Items from the DFAQ-CU ^45^
Sociodemographics	Items taken from the WHO Disability Assessment Schedule (WHODAS-II) ^46^
Social situation and participation	Custom-made items
Clinically relevant psychological symptoms	Brief Symptom Inventory (BSI-18) ^47^
Quality of life	EQ5D ^48^
Use of tobacco, alcohol, and other drugs	Custom-made items, AUDIT-C ^49^, use items from EuropASI ^50^
Risky cannabis use/possible cannabis use disorder	CUDIT-R ^51^
Chronic diseases and their treatment	Custom-made items
Utilization of addiction services (counselling, prevention, therapy), for economic evaluation	Custom-made items
Satisfaction and acceptance of the dispensary model	Custom-made items
Adverse events related to using cannabis	Custom-made items

At T18, we will conduct a post-intervention assessment of intervention group participants to examine how their cannabis use has developed after being denied further legal purchases of cannabis products. This assessment will include all instruments outlined in
Table 2, in addition to several free-text items.

There will be three main types of study data: (1) chemical analyses of standard consumption units, (2) sales data, (3) survey responses of participants. For (1), we will adhere to the standard operating procedures issued by the BfArM
^42^. For (3), we will aim to carry out digital survey assessments to minimize human error in data entry. Further, consistency checks will be performed before data analyses.

